### Data collection and management

2.11

Data will be collected at the following time points: (1) baseline assessment (T0): conducted prior to the first training, including CPR knowledge score, skills performance score, self-efficacy (recognition and evaluation), and behavioral intention; (2) immediate post-first training assessment (T1): conducted immediately after the first training session, including CPR knowledge score, skills performance score, self-efficacy (recognition and evaluation), behavioral intention, and course satisfaction; (3) 3-month post-first training assessment (T2), conducted prior to the second training session, including CPR knowledge score, skills performance score, self-efficacy (recognition and evaluation), and behavioral intention; (4) immediate post-second training assessment (T3): conducted immediately after the second training session, including CPR knowledge score, skills performance score, self-efficacy (recognition and evaluation), behavioral intention, and course satisfaction; (5) 3-month post-second training follow-up (T4), only questionnaires will be collected, including CPR knowledge score, skills performance score, self-efficacy (recognition and evaluation), behavioral intention, course satisfaction, and skill retention rate. The skills performance scores will be assessed by instructors who rotate across the four classes, such that each instructor trains and evaluates the skills for all classes in turn. This rotation minimizes rater bias and ensures consistency and fairness in skill assessment.

All data will be collected and managed using an electronic data capture platform (e.g., Wenjuanxing). Each participant will be assigned a unique identification code (ID), and all data will be anonymized. Data will be stored in encrypted formats, with access restricted to the research team to ensure participant privacy and data security. Logical checks and outlier alerts will be implemented during data entry to enhance data quality.

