**Methods:**

A single-blind cluster randomized controlled trial with a 2 × 2 factorial design will be conducted in a middle school in Hohhot, Inner Mongolia Autonomous Region. A total of 160 eligible middle school students will be recruited and randomly assigned in a 1:1:1:1 ratio to four groups: conventional CPR training group, manikin-based training group, scenario-based drama review group, and combined manikin-based training plus scenario-based drama review group. Each training session will last 90 min. The primary outcomes are CPR-related knowledge score and skill performance score. Secondary outcomes include self-efficacy (behavioral performance and evaluation), behavioral intention, course satisfaction, and skill retention rate. Data will be collected at Baseline assessment (T0), immediate post-first training assessment (T1), 3-month post-first training assessment (T2), immediate post-second training assessment (T3), 3-month post-second training follow-up (T4).

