#### Blinding of participants and intervention providers

2.9.1

This study employed a cluster randomized controlled design. Participants were not informed of the specific differences between the study groups, such as whether they received simulation-based training or scenario-based role-playing training. However, intervention providers were aware of the intervention content and therefore could not be blinded. This limitation is inherent to the study design.

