#### Blinding of outcome assessors

2.9.2

All outcome assessments were independently conducted by two emergency medicine instructors who had received standardized training. These assessors were not involved in group allocation, intervention implementation, or data management. In addition, they had no access to participants’ group assignments or previous assessment results during the evaluation process. Practical skills were evaluated using standardized scoring criteria, while questionnaire data were collected anonymously. Data entry, management, and statistical analyses were performed by designated research personnel who remained blinded to group allocation throughout the study.

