### Data analysis plan

2.13

This study adopted a 2 × 2 factorial cluster randomized controlled trial design, with class as the unit of random allocation and individual students as the unit of analysis. All statistical analyses will account for clustering at the class level and the correlation among repeated measurements from the same participant. Three analysis sets will be predefined: the full analysis set, the per-protocol set, and the safety analysis set. The full analysis set will serve as the primary analysis population and will include all randomized participants, who will be analyzed according to their originally assigned groups, following the intention-to-treat principle. Participants will not be excluded from the primary analysis because of intervention non-completion, absence from training sessions, or withdrawal during the intervention period, nor will their originally assigned group be changed. The per-protocol set will be used for robustness analyses and will include only participants who complete the predefined core intervention components and complete the primary outcome assessment. The safety analysis set will include participants who receive at least one intervention session or participate in at least one training activity, and will be used for descriptive analyses of adverse events and safety-related information. Two binary intervention factors are specified: Factor 1, initial training method, including lecture-only training versus lecture plus manikin practice; and Factor 2, booster reinforcement method, including traditional review versus scenario-based simulation. The four factorial groups correspond to Classes 13, 1, 10, and 12, respectively.

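### Sections 2.9.2 and 2.11 contradict each other on who scores the primary skills outcome: two blinded assessors who do no training, or the trainers themselves

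*Protocol article*

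**What the plan says.** The Abstract (Methods) makes skills one of two primary outcomes: "The primary outcomes are CPR-related knowledge score and skill performance score".

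Section 2.9.2 (Blinding of outcome assessors) describes one arrangement: "All outcome assessments were independently conducted by two emergency medicine instructors who had received standardized training". It continues: "These assessors were not involved in group allocation, intervention implementation, or data management". It adds that they had no access to participants' "group assignments or previous assessment results during the evaluation process", and that data entry and analysis staff also stay blinded.

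Section 2.11 (Data collection and management) describes another: "The skills performance scores will be assessed by instructors who rotate across the four classes", so that "each instructor trains and evaluates the skills for all classes in turn". It gives reduced rater bias as the reason for rotating.

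On the blinding of trainers, section 2.9.1 says: "intervention providers were aware of the intervention content and therefore could not be blinded". Section 2.4.2 names the intervention implementers as the only people with access to the allocation. Section 2.5 counts eight instructors for 160 participants.

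There is one class per arm (2.4.2), and section 2.13 prints the class numbers: "The four factorial groups correspond to Classes 13, 1, 10, and 12, respectively".

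**The concern.** A person who trains the classes is involved in delivering the intervention, so the two descriptions of the skills rater exclude each other. A reader cannot tell whether a primary outcome is rated blind or by the unblinded people who taught the students.

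Under 2.11, each rater has taught every class and each class is one arm. The rater would therefore know which training the student being scored had received. Any tendency to score according to expectation would follow the arm, and so would the training effect. None of the models in 2.13 could separate the two. Unblinded live scoring also cannot be repaired afterwards unless the performances were recorded.

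**Working it through.** The point rests on text, so the check sets the two sections side by side.

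| Question | Section 2.9.2 | Section 2.11 |
|---|---|---|
| Who scores skills? | Two emergency medicine instructors, for all outcomes | Instructors rotating over the four classes |
| Do they also train? | No | Yes, every class |
| Do they know the allocation? | No | Yes, by 2.4.2 and 2.9.1 |
| Protection offered | Independence and blinding | Rotation |

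**Can the two be reconciled?** Four readings were tried.

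1. *The two assessors belong to the eight-person training team.* They would then deliver training, which 2.9.2 rules out.
2. *Section 2.11 means informal evaluation in class.* Its sentence is about the skills performance scores, the term it uses for the outcome listed at each time point.
3. *Section 2.9.2 covers the other outcomes only.* It says all outcomes and goes on to mention how practical skills are scored.
4. *Instructors score only classes they did not train.* Section 2.11 has each of them train and evaluate all classes.

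None of the four works.

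**Which scores are exposed if 2.11 is followed?**

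- T0 is not. Baseline precedes allocation (2.3) and the first training (2.11).
- Skills scores from T1 onward are.
- The retention rate (2.8.6) is also exposed, because it divides one post-training skills score by another. It would be unaffected only if both scores were shifted in the same proportion, and nothing in the plan ensures that.
- The knowledge score has little exposure. It is nine multiple-choice items with a fixed key (2.8.1).

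**Does rotation help?** If every rater scores every class, a severe or lenient rater affects all arms alike. An expectation shared by the raters about the manikin or drama classes is not balanced in this way. The reliability checks in 2.9.3 (intraclass correlation thresholds and 5% repeat scoring) measure agreement, and raters who share a bias can agree well.

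**How large could the effect be?** The protocol gives no figure for rater bias and no range or standard deviation for the skills score. The 15-point difference and the SD of 15 in 2.10 belong to the combined knowledge and skills score rate. An illustration can therefore only be given in SD units of the skills score. Assume no true effect and a scoring shift of b SD in favour of one level of a factor, with 80 against 80 students, a two-sided 5% test, a normal approximation and clustering ignored.

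- Standard error in SD units: √(2/80) = 0.158.
- Rejection rate: 1 − Φ(1.96 − b/0.158) + Φ(−1.96 − b/0.158).
- b = 0.1 gives about 10%, b = 0.2 about 24%, and b = 0.3 about 48%, against a nominal 5%.

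The values of b are assumptions. The figures show how sensitive the test would be to such a shift. They do not estimate a bias in this trial.

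**The case against.** The strongest reply is that 2.9 is the section devoted to blinding and is specific about it: two trained assessors, independence, no access to allocation, and an agreement threshold to be met before formal scoring. On that view the 2.11 sentence is a leftover and the trial is sound. That may be so, but the document does not say it. Section 2.11 is just as specific and gives its own reason for using trainers.

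Several stronger readings are tempting, and the documents do not support them.

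- *The skills outcome is in fact rated by unblinded trainers.* This follows only if 2.11 describes practice, which is the open question.
- *The bias favours the enhanced arms, because trainers have a stake in the result.* The protocol gives no evidence on direction and states no such stake. The skills criteria in 2.8.2 come from a cited source that is not shown, so how much judgement they leave to the rater is also an inference.
- *A few points of leniency would account for a given share of the planned 15-point difference.* That difference is on the combined scale, where the keyed knowledge test would dilute a shift in skills by an amount that depends on unstated weights.
- *The analysts are unblinded because the class numbers are printed.* Section 2.9.2 says they stay blinded, 2.11 says data are coded and anonymised, and 2.13 does not list the four groups beside the class numbers. Knowing the class could break the blinding; the text does not show that it has.
- *Every performance is filmed.* Section 2.9.3 mentions videos only for a 5% repeat check.

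With these set aside, the contradiction about who scores skills remains in full.

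**Conclusion.** The protocol is wrong as written: 2.9.2 and 2.11 cannot both describe the scoring of a primary outcome. If 2.11 holds, skills scores from T1 onward and the retention rate are rated by unblinded trainers, and an expectation bias could not be told apart from a training effect. In that case the statement that rotation minimises rater bias is unsupported, because rotation addresses severity and not knowledge of the arm. The size and direction of any bias are unknown, and the conclusion does not depend on the illustrative figures. It rests on the wording of 2.4.2, 2.9.1, 2.9.2 and 2.11 and on there being one class per arm. The risk to analyst blinding is secondary and only potential.

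**What to change.** First state which arrangement applies. Deleting the 2.11 sentence without doing so could hide the problem if that sentence describes practice.

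Then replace the sentence along these lines: *At each time point where skills are tested, they are scored only by the two assessors described in 2.9.2, who deliver no training.* The same edit should settle T4, which 2.11 describes as questionnaire-only while listing a skills score and the retention rate.

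If trainers do score skills, withdraw the assessor-blinding statement for that outcome and the rater-bias claim, and report unblinded scoring as a limitation.

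Where performances are filmed, the two assessors can score the recordings with class identity hidden and in an order mixed across classes. This is one good option; the reconciliation itself is what is required.

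Give the analyst masked class and arm codes. Class must enter the model in 2.13, but its real number need not.

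**Cost.** The wording is free, but the assessors' time is not. At about 15 minutes per participant (2.5), a round takes 160 × 15 / 60 = 40 station-hours, or 20 hours each if the two assessors split the students over the two assessment manikins. If they score recordings instead, someone else must run the stations, video must be handled, and scores arrive later.

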### Data monitoring and quality assurance

2.12

As this study primarily involves CPR skills training, appropriate safety measures will be implemented during each training session to ensure that students are not injured during simulated practice. All participants will perform CPR under the supervision of experienced instructors to ensure safety. Trial monitoring will be conducted by a supervisory team from the coordinating center, which operates independently of the on-site investigators and reports to the steering committee. The data management system will automatically validate input data. If any recorded values fall outside acceptable ranges, warning messages will be generated, prompting users to verify and correct the entries.

### Data analysis plan

2.13

This study adopted a 2 × 2 factorial cluster randomized controlled trial design, with class as the unit of random allocation and individual students as the unit of analysis. All statistical analyses will account for clustering at the class level and the correlation among repeated measurements from the same participant. Three analysis sets will be predefined: the full analysis set, the per-protocol set, and the safety analysis set. The full analysis set will serve as the primary analysis population and will include all randomized participants, who will be analyzed according to their originally assigned groups, following the intention-to-treat principle. Participants will not be excluded from the primary analysis because of intervention non-completion, absence from training sessions, or withdrawal during the intervention period, nor will their originally assigned group be changed. The per-protocol set will be used for robustness analyses and will include only participants who complete the predefined core intervention components and complete the primary outcome assessment. The safety analysis set will include participants who receive at least one intervention session or participate in at least one training activity, and will be used for descriptive analyses of adverse events and safety-related information. Two binary intervention factors are specified: Factor 1, initial training method, including lecture-only training versus lecture plus manikin practice; and Factor 2, booster reinforcement method, including traditional review versus scenario-based simulation. The four factorial groups correspond to Classes 13, 1, 10, and 12, respectively.

The research team will strictly record and distinguish participants who withdraw during the intervention period, defined as participants who stop receiving the assigned training content after randomization; those who do not complete the intervention, defined as participants who fail to meet the predefined core course completion criteria; those who are absent from one or more scheduled training sessions; and those lost to follow-up, defined as participants who do not complete the outcome assessments at the prespecified time points. For participants who do not complete the intervention or are absent from training sessions, the research team will still make every effort to collect subsequent outcome data, unless the participant or their guardian explicitly withdraws consent for continued participation or further data collection. The primary analysis will continue to follow the intention-to-treat principle, whereby all randomized participants will be included in the analysis according to their originally assigned groups. Per-protocol analysis will be conducted as a sensitivity analysis to assess the influence of intervention adherence on the study findings.

Baseline characteristics will be summarized by study group. Continuous variables will be presented as means and standard deviations or medians and interquartile ranges, depending on their distribution. Categorical variables will be presented as frequencies and percentages. Baseline variables with important clinical or educational relevance, as well as variables showing apparent imbalance across study groups, will be adjusted for as covariates in subsequent models.

Continuous outcomes will be analyzed using linear mixed-effects models. Binary outcomes will be analyzed using generalized linear mixed-effects models, and ordinal outcomes will be analyzed using ordinal logistic mixed-effects models. The models will include both fixed and random effects. Fixed effects will include the two intervention factors, time, the interaction between the two intervention factors, the interactions between each intervention factor and time, and the three-way interaction among the two intervention factors and time. When necessary, baseline outcome values and other prespecified covariates will also be included. Random effects will include a class-level random intercept to account for the correlation among students within the same class, as well as an individual-level random intercept to account for the correlation among repeated measurements from the same participant over time.

For repeated-measures data, within-participant correlation will be addressed through the inclusion of an individual-level random intercept. If the number of measurement time points and sample size allow, an unstructured covariance structure will be prioritized. If the model fails to converge or parameter estimates are unstable, compound symmetry or first-order autoregressive covariance structures will be considered as alternatives. The final model will be selected based on model fit indices and study design considerations. Model selection will consider the Akaike information criterion, Bayesian information criterion, model convergence, and the interpretability of parameter estimates.

Factorial effects will be analyzed according to the principle of interaction-first interpretation. For the primary outcome, the interaction between the two intervention factors and the three-way interaction among the two intervention factors and time within the repeated-measures framework will first be tested. If the interaction is statistically significant or shows a practically meaningful trend, simple-effects analyses will be conducted to estimate the effects of different intervention combinations at each time point. If no clear interaction is observed, the main effects of the two intervention factors will be interpreted. For intervention effects that vary over time, the interaction terms between intervention factors and time will be treated as key parameters for evaluating changes in intervention effects.

Adjusted effect estimates and their 95% confidence intervals will be reported. For continuous outcomes, between-group mean differences or standardized effect sizes will be reported. For binary outcomes, odds ratios or relative risks with 95% confidence intervals will be reported. For ordinal outcomes, corresponding ordinal odds ratios will be reported. The intraclass correlation coefficient and design effect will be calculated to quantify clustering effects. The robustness of the results will be examined through per-protocol analysis and multiple imputation.

For missing data, the number, proportion, and reasons for missingness will first be reported by study group. If outcome data are missing, multiple imputation will be performed under the missing-at-random assumption. Each imputed dataset will be analyzed separately, and the estimates will then be pooled. To assess the potential impact of post-randomization differential attrition on the study conclusions, sensitivity analyses will be conducted. If there are apparent differences across study groups in intervention-period withdrawal rates, absence rates, intervention non-completion rates, or loss-to-follow-up rates, their potential contribution to selection bias and their possible influence on estimates of intervention effects will be discussed in the interpretation of the results.

Given that this is a pilot study, the sample size was primarily determined based on implementation feasibility. A lack of statistical significance in interaction tests will not necessarily rule out the presence of practically meaningful interaction effects. Therefore, the findings will be interpreted comprehensively by considering effect sizes, confidence intervals, intervention adherence, and implementation feasibility. All statistical tests will be two-sided, and a *p* value of < 0.05 will be considered statistically significant. Statistical analyses will be conducted using SPSS 27.0 and R 4.5.2 (packages lme4, emmeans, and mice).

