#### Stage 1: selection of eligible classes

2.4.1

First, among a total of 16 classes that meet the inclusion criteria within the school, 4 target classes will be randomly selected using Microsoft Excel. The procedure is as follows: a new worksheet will be created, with Column A assigned numbers from 1 to 16 as unique identifiers for each class. In Column B, the formula = RAND() will be used to generate random numbers for each class. These random numbers will then be copied and pasted as values to prevent subsequent changes. All classes will then be sorted in ascending order based on the values in Column B, and the first 8 classes will be selected as the study sample.

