### Study arms

2.6

All participants will receive standardized conventional CPR training. Based on random allocation, participants will then receive different forms of enhanced training or review interventions. Middle school students will be randomly assigned to one of the following four groups:

Group A (Manikin-based training + scenario-based drama review):

Phase 1: following conventional CPR video demonstration and theoretical instruction, students will undergo manikin-based CPR skills training, practicing key steps such as compression depth, rate, and rescue breathing under instructor guidance.

Phase 2: scenario-based drama review will be conducted by simulating emergency situations (e.g., sudden collapse on campus). Students will engage in role-playing (rescuer, bystander, caller for help) and complete the CPR procedure within these scenarios to reinforce skill application and emergency response capacity.

Group B (Manikin-based training only):

Phase 1: following conventional CPR video demonstration and theoretical instruction, students will receive manikin-based CPR skills training, focusing on repeated practice of compression depth, rate, and ventilation under instructor guidance. Phase 2: conventional CPR training (theoretical explanation and demonstration) will be provided.

Group C (scenario-based drama review only):

Phase 1: students will complete conventional CPR video demonstration and theoretical instruction without manikin-based practice. Phase 2: scenario-based drama review will be conducted through simulated emergency situations (e.g., sudden collapse on campus), with students participating in role-playing and completing CPR procedures to enhance practical application and emergency response skills.

Group D (control group):

Phase 1: students will complete conventional CPR video demonstration and theoretical instruction. Phase 2: conventional CPR theoretical instruction and standard procedural demonstration will be provided.

To ensure consistency across groups, all training sessions will be delivered by uniformly trained instructors. The duration and overall instructional framework will be standardized, with differences limited to the inclusion or exclusion of manikin-based training and scenario-based drama review. The detailed study flowchart is presented in Figure 1.

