### Sample size calculation

2.10

This study is a two-factor factorial cluster randomized controlled trial, with “CPR knowledge and skills scores” as the primary outcome. Based on the literature, a significance level of 5% (*α* = 0.05) and a statistical power of 80% (*β* = 0.20) were adopted. Sample size estimation was informed by data from previous studies. It was assumed that the mean total CPR score (combined knowledge and skills score rate) would be 80% in the intervention group and 65% in the control group, with a standard deviation of 15% in both groups, corresponding to an effect size of *d* = 1.0. Assuming a 15% difference in the primary outcome (main effect), G*Power 3.1 was used for sample size calculation, indicating that a total of 128 participants would be sufficient for multivariate regression analysis (effect size = 0.25, power = 0.80, critical *F* = 3.921). Considering a potential attrition rate of 20%, the final minimum sample size was set at 160 participants. This study also takes into account the design effect resulting from the correlation among subjects within clusters. The design effect is calculated using the formula DE = 1 + (m − 1)*ρ*, where m represents the average number of subjects per cluster, and ρ represents the intracluster correlation coefficient (ICC) (17). In cluster randomized trials, the design effect is commonly used to adjust the sample size required for an individual randomized trial to the sample size required for a cluster-randomized design. The final minimum sample size for this study was set at 160 participants, which represents a 25% overall inflation factor added to the 128 participants required at the individual level. This inflation factor accounts for both the cluster-randomized design effect and the potential impact of dropouts or invalid data. Based on the average cluster size in this study and the ICC estimated from previous similar studies, the design effect did not exceed 1.25 (18). Therefore, after adjusting for the design effect, a sample size of 160 participants (selecting 4 classes, with 40 participants per class) would still provide no fewer than 128 valid cases, thereby meeting the requirements for testing the primary effect.

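### Fitting the drama factor at visits before any drama review saturates the model at class level, so the manikin effect at T1 and T2 has no estimable class-level standard error, although the design leaves 2 degrees of freedom for one

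*Protocol article*

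**What the plan says.** Section 2.10 sizes the trial as "selecting 4 classes, with 40 participants per class", and section 2.13 adds that "The four factorial groups correspond to Classes 13, 1, 10, and 12, respectively". That is one class per factorial cell. Section 2.4.2 also allocates four classes, one to each group. One sentence in section 2.4.1 disagrees: "the first 8 classes will be selected as the study sample".

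Section 2.13 defines "Factor 1, initial training method, including lecture-only training versus lecture plus manikin practice" and "Factor 2, booster reinforcement method, including traditional review versus scenario-based simulation". In Study arms (2.6), Groups A and B both have lecture plus manikin practice in Phase 1. Groups C and D have the lecture only; for Group C, "students will complete conventional CPR video demonstration and theoretical instruction without manikin-based practice". Drama review appears only in Phase 2, for A and C. Section 2.11 places T2 before the second training session.

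On the model, section 2.13 says: "Fixed effects will include the two intervention factors, time, the interaction between the two intervention factors". It then adds each factor by time, the three-way term, a class random intercept and a student random intercept. No term is restricted by visit. The interaction and three-way terms are tested first. The same section promises that all analyses will account for class clustering and that the intraclass correlation and design effect will be calculated.

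**The concern.** Before the booster, A and B have had the same training, and so have C and D. For the manikin question at T1 and T2 the design therefore has two classes on each side, and the differences A-B and C-D show how far classes differ with no difference in treatment. The stated model instead labels those differences as Factor 2 and interaction effects. Nothing is left at class level against which to judge the manikin effect.

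Two things are at stake. First, the standard error of the manikin effect at T1 and T2 is whatever the software settles on for a class variance that the data do not inform. If that is zero, class differences are read as training effects. Second, the interaction-first tests span all visits, so pre-booster class differences can feed into the decision to report simple effects, and readers lose a yardstick for how much of a T3 or T4 difference could be class alone.

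**Working it through.** **Inputs.** From the documents: 4 classes of 40; 20% attrition; two-sided 5% level; 80% versus 65% with SD 15% (d = 1.0); G*Power effect f = 0.25; design effect at most 1.25 (sections 2.10 and 2.13). Derived: 160 × 0.8 / 4 = 32 analysable students per class; ICC bound 0.25/39 = 0.0064 at 40 per class; d = 2f = 0.5 for a two-level factor. Assumed: ICC 0.05 and 0.10.

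**The plan's own figure.** With f = 0.25, 1 numerator df, four groups and a 5% level, N = 128 gives power 0.801, and 128/0.8 = 160. Both reproduce. Critical F is 3.918 against the stated 3.921, a trivial difference.

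**Saturation.** Four classes by five visits give 20 class-by-visit cells.
- As written: 5 time terms + 5 Factor 1 + 5 Factor 2 + 5 interaction = 20. Rank 20 of 20, nothing left.
- Without Factor 2 and the interaction at T0, T1 and T2 (6 terms): rank 14.
- Also without Factor 1 at T0, before any training: rank 13, leaving 7 df, 3 of them for the class intercept.

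At T1 or T2 alone, four class means leave 0 df under both factors plus interaction, 1 df under both factors without interaction (t critical 12.71), and 2 df under Factor 1 alone (t critical 4.303).

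**What saturation does.** In one simulated visit (four classes of 40, student SD 15), the REML log-likelihood under the saturated model was -512.4636 at every class variance tried from 0 to 200, while the SE of the manikin effect ran from 2.37 to 14.34 points. With Factor 1 alone, the likelihood did vary with class variance (-529.8 at 0, -518.7 at 50), so the variance is estimable. The manikin estimate was 13.488 in both models.

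**Type I error if class variance is set to zero, single visit, 32 per class.** In SD units a class mean has variance v = ICC + (1 - ICC)/32. The two-versus-two difference has variance v/2 + v/2 = v. Type I error = 2[1 - Φ(1.98 × s/√v)], where the student-level SE s is √(1/32) = 0.177 (total SD) or √((1 - ICC)/32) (within-class SD).

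| ICC | √v | Type I, total SD | Type I, within-class SD |
|---|---|---|---|
| 0.0064 | 0.194 | 7% | 7% |
| 0.05 | 0.282 | 21% | 23% |
| 0.10 | 0.358 | 33% | 35% |

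**The same for change from T0.** Assume a within-student correlation of 0.5 and that a share k of class variance persists. The student-level variance is (1 - ICC)/32; the true variance adds 2 × ICC × (1 - k).

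| k | ICC 0.05 | ICC 0.10 |
|---|---|---|
| 1.0 | about 5% | about 5% |
| 0.8 | 0.0297 against 0.0497: 13% | 0.0281 against 0.0681: 20% |
| 0.5 | 0.0297 against 0.0797: 23% | 0.0281 against 0.1281: 35% |

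**The 2-df class-level test.** Over 20,000 simulations at 40 per class with normal class effects, its size was 0.050, 0.048 and 0.051 at the three ICCs. Unadjusted power at 32 per class, from the noncentral t with 2 df and noncentrality d/√v:

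| ICC | d = 1.0 | d = 0.5 |
|---|---|---|
| 0.0064 | 74% | 31% |
| 0.05 | 48.5% | 18.5% |
| 0.10 | 35% | 14% |

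Four classes split two and two give 6 allocations, so an exact two-sided permutation p cannot fall below 2/6 = 0.33.

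**The case against.** The strongest reply is that the root defect is one class per cell, and this repair is a low-power salvage of one factor at two visits. That stands: at d = 0.5, the effect that sized the trial, power is 14 to 31%, and drama and the interaction gain no inference.

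Several stronger readings are tempting, and the documents do not support them.
- A reader might infer that the pre-booster A-B and C-D differences are the only information on class variation. They are not. Section 2.11 collects knowledge and skills at T0, and four untreated class means carry 3 df.
- A reader might infer that the planned analysis will reject at the 7, 21 and 33% rates. The plan does include a class random intercept, so its standard error is undetermined rather than necessarily student-level. Those rates need class variance set to zero and a single-visit comparison. Section 2.13 treats factor-by-time terms as key, and a class effect constant over time cancels in change from T0.
- A reader might infer that the manikin comparison itself is lost. Only its error term is; the estimate is the same.
- A reader might take the 2-df test as exact. It needs normal class means with equal variance.

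A mixed model restricted by visit and using T0 to T2 jointly is a defensible alternative, but it assumes that class effects are stable over time. The main-effects fallback in section 2.13 does not remove the problem: it does not say that the interaction is dropped, and dropping it alone leaves 1 df.

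**Conclusion.** The point holds in this form. On four classes, the fixed effects in section 2.13 include terms that cannot be intervention effects before T3. They exhaust the class-level information, so the promised class random intercept, intraclass correlation and design effect cannot be estimated, and the manikin standard error at T1 and T2 is not determined by the data. Removing those terms leaves 2 class-level df for that comparison at either visit.

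The size is conditional: 7% at the plan's own ICC bound, and 21 to 23% or 33 to 35% at assumed ICCs of 0.05 or 0.10, for a single visit with class variance set to zero. For change from T0 it runs from about 5% upward, depending on how far class effects shift between visits.

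Two readings of the documents underlie this. One is four classes rather than the eight in section 2.4.1; eight classes, two per cell, would leave class-level df, so the sections must be reconciled. The other is that Phase 2 is the second training session, which follows from sections 2.6, 2.11 and 2.13 together but is not stated in one sentence.

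**What to change.** In section 2.13:
1. Set Factor 2 and all its interactions to zero at T0, T1 and T2.
2. Test Factor 1 at T1 and at T2 as A+B versus C+D with class-level error on 2 df, using change from T0 or T0 adjustment at student level. A class-level T0 covariate would cost one of the 2 df.
3. Report the T0 class differences, and A-B and C-D at T1 and T2, as negative controls beside every T3 or T4 drama or interaction estimate, and state that those estimates remain confounded with class.
4. Reconcile the class count in section 2.4.1 with sections 2.4.2, 2.10 and 2.13.

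The cost is wording only: no new classes, visits or data. The plan should state the downsides: wider intervals for the manikin effect than a student-level analysis would print, reliance on normal class means with equal variance, no permutation test able to reach 5%, and the power shown above, including that at d = 0.5.
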